### Statistical analysis

The data obtained in this study will be analyzed with SPSS software, version 20.0. The reliability of the model and validity of the hypothesis will be checked and the normal distribution of variables, residuals values and homogeneity of the variances will be studied. The normal distribution of variables will be verified by the Kolgomorov-Smirnov test for continuous variables and the Chi-Square Goodness of Fit test for categorical variables. Residuals will be analyzed using the residuals graph to compare observed values against the residuals values, distribution and tendency. Linearity will be examined using bivariate scatter plots of observed residual values against expected values.

Descriptive statistics will be used first to characterize the study group. The outcomes will be reported with the mean and standard deviation of scores at baseline, post-treatment and follow-up time. To evaluate the main effect of the independent variable (interventions) on outcomes and potential time-by-treatment interactions, repeated measures analysis of variance (RM ANOVA) will be conducted. To check for sphericity, the variances of the differences between all combinations of groups of within-subjects factors will be analyzed with the Mauchly test and verified by the local invariant test. Although the Mauchly test is the most widely used, both tests will be performed because some authors have reported that the local invariant test produces fewer Type II errors than the Mauchly test with small sample sizes and a large number of variables. The Levene test will be used to assess the equality of variances at the 0.05 significance level. Post hoc analyses of significant group x time interaction effects will be carried out using the Tukey multiple comparison procedure to examine pairwise comparisons of the groups’ means for all outcome measures and across the three data collection times.

To complete the analysis, the effect size and level of significance for interacting effects (group × time) will be shown, using Cohen’s d (standardized difference between two means). The interpretation of effect size will be made following the guidelines of ≥ 0.2 as small effect, ≥ 0.5 as medium effect, and 0.8 and above as large effect, in accordance with Cohen. If normality and homoscedasticity assumptions are violated, data transformation and non-parametric procedures will be considered. Data from drop-outs and patients who discontinued intervention will be analyzed following an intention-to-treat principle. A P value of 0.05 will be used for statistical significance.

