## Methods/Design

### Research design

This study will be conducted as a two-arm patient and therapist-blinded, parallel, randomized controlled trial design, following the recommendations of the SPIRIT guidelines (Additional file 1) [30]. The experimental group will receive a combined functional rehabilitation program at home and will be compared to a control group receiving a conventional health education program. The main outcome measures will be collected at three time points over a 16-week period: (1) at baseline, (2) at posttreatment (that is, 8 weeks after baseline), and (3) at follow-up (16 weeks after baseline). The study assessment schedule is shown in Table 1. The study was approved on 26 May 2014 by the Investigation Ethics Committee of Granada province-CEI (Andalusian Health Service, Granada, Spain, 180SP) and complies with the 2013 modification of the Helsinki Declaration [31] and with current Spanish legislation for clinical trials [32].

**Table 1 Tab1:** Schedule of enrollment, interventions, and assessments of the study

	Enrollment	Allocation	Post-allocation		
Time point	Pre-treatment	Time 0	Baseline	8-weeks posttreatment	2-month follow-up
Enrollment:					
Eligibility screen	X				
Informed consent	X				
Allocation		X			
Interventions:					
Combined functional rehabilitation of apraxia group			X	X	
Traditional health educative protocol group			X	X	
Assessments:					
Sociodemographic and clinical data			X		
Barthel index			X	X	X
Instrumental Activities of Daily Living Scale			X	X	X
Observation and scoring of ADL-Activities			X	X	X
De Renzi Test for ideational apraxia			X	X	X
De Renzi Test for ideomotor apraxia			X	X	X
Recognition of gestures			X	X	X
Test of upper limb apraxia (TULIA)			X	X	X
Quality of life scale for stroke (ECVI-38)			X	X	X

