### Sample size

Based on previously published findings on the use of rehabilitation treatments by poststroke patients with upper limb apraxia [14], a clinically important difference pre-post treatment of 2.44 points on the Barthel Index for ADLs (primary outcome) was used to calculate the sample size required to detect the increase in patients’ functional ability with combined functional rehabilitation (experimental group) versus the traditional health educative protocol (control group), using the PASS 13 (Power Analysis and Sample Size) program (http://www.ncss.com/). A sample size of 15 patients per arm was estimated to provide a 95 % confidence interval (CI) with a power of 80 %, assuming a standard deviation of 3.10 points for this difference and a two-sided test (α) of 0.05. The sample size has been increased to a total of 40 to allow for a loss to follow-up of up to 22 %.

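### The Barthel analysis names a baseline-diluted group main effect and an omnibus interaction without ranking them, and reaches the week-8 difference only post hoc; one baseline-adjusted week-8 contrast should be primary

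*Protocol article*

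**What the plan says.** Under Research design, "The main outcome measures will be collected at three time points over a 16-week period": baseline, week 8 (end of treatment) and week 16 (follow-up).

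Under Sample size, the trial is sized on "a clinically important difference pre-post treatment of 2.44 points on the Barthel Index for ADLs (primary outcome"), experimental versus control, "assuming a standard deviation of 3.10 points for this difference", with "a two-sided test (α) of 0.05" and "with a power of 80"%. This gives 15 patients per arm, raised to 40 in total for up to 22% loss.

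Under Statistical analysis, the method for all outcomes is: "To evaluate the main effect of the independent variable (interventions) on outcomes and potential time-by-treatment interactions, repeated measures analysis of variance". Group means are compared visit by visit only through Tukey post hoc tests, and only where the group-by-time interaction is significant. Cohen's d and the significance level are then reported for the interaction. The threshold is general: "A P value of 0.05 will be used for statistical significance". No primary visit is named, neither effect is designated as primary, and no adjustment for baseline is stated.

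**The concern.** Three quantities are in play and they are not the same: the group effect averaged over all three visits, any departure from parallel profiles across the visits, and the between-arm difference in change from baseline to week 8. The sample size section describes the third. The analysis section tests the first two and leaves the third to a gated follow-up.

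Randomised arms have no expected difference at baseline, so including baseline in the group average can only pull a treatment effect towards zero. The interaction does not have that fault, but a significant result does not show at which visit the arms differ, and its power depends on the course after treatment ends. With at most 40 patients, the choice of test affects both the chance of detecting a real benefit and what a positive result can be said to show. Leaving two unranked tests on one primary outcome also leaves the success rule open.

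**Working it through.** **Inputs.** From Sample size: difference 2.44, SD of change 3.10, two-sided 0.05, 15 evaluable per arm (20 randomised per arm). The between-visit correlation ρ is not given. I assume it is equal for all visit pairs, with equal variances, over the range 0.3 to 0.9. The per-visit SD is then σ = 3.10/√(2(1−ρ)): 3.10, 4.00, 4.90 and 6.93 at ρ = 0.5, 0.7, 0.8 and 0.9.

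**The plan's own figure.** A between-arm t-test of change with these inputs needs 27 per arm (26 by normal approximation). At 15 per arm its power is 55%, and at 20 per arm 68%. The stated 15 reproduces only as a one-sample paired test of change within one arm (power 80.9%). The inflation does reproduce: 15/0.78 = 19.2, so 20 per arm.

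**Group main effect.** If the benefit is sustained, the expected difference is (0 + 2.44 + 2.44)/3 = 1.63. If half is lost by week 16 it is (0 + 2.44 + 1.22)/3 = 1.22, and if all is lost, 2.44/3 = 0.81. The SD of a patient's three-visit mean is σ√((1+2ρ)/3): 2.53, 3.58 and 4.56 at ρ = 0.5, 0.7 and 0.8. Power is from the noncentral t with 2n−2 df.

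**Interaction (2 and 2(2n−2) df).** The noncentrality is λ = (n/2)·Σ(eⱼ−ē)²/(σ²(1−ρ)), where eⱼ is the effect at visit j and σ²(1−ρ) = 3.10²/2 = 4.805, so ρ drops out.
- Sustained: Σ = 1.627² + 2 × 0.813² = 3.97. At n = 20, λ = 10 × 3.97/4.805 = 8.26 and power is 71%. At n = 15, λ = 6.20 and power is 57%.
- Half lost: Σ = 2 × 1.22² = 2.98. At n = 20, λ = 6.20 and power is 58%. At n = 15, λ = 4.65 and power is 45%.
- All lost by week 16: Σ is again 3.97, so power is the same as for a sustained benefit. The omnibus test alone does not tell these courses apart.

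**Week-8 ANCOVA.** The residual SD is σ√(1−ρ²) = 3.10√((1+ρ)/2): 2.68, 2.86, 2.94 and 3.02 at ρ = 0.5, 0.7, 0.8 and 0.9, with 2n−3 df. Week 16 does not enter.

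| Power | ρ 0.5 | ρ 0.7 | ρ 0.8 | ρ 0.9 |
|---|---|---|---|---|
| 20 per arm: main effect, sustained | 51% | 29% | 20% | 12% |
| 20 per arm: main effect, half lost | 32% | 18% | 13% | 9% |
| 20 per arm: interaction, sustained / half lost | 71 / 58% | 71 / 58% | 71 / 58% | 71 / 58% |
| 20 per arm: change score, week 8 | 68% | 68% | 68% | 68% |
| 20 per arm: ANCOVA, week 8 | 80% | 75% | 72% | 70% |
| 15 per arm: main effect, sustained | 40% | 22% | 16% | 10% |
| 15 per arm: interaction, sustained / half lost | 57 / 45% | 57 / 45% | 57 / 45% | 57 / 45% |
| 15 per arm: change score, week 8 | 55% | 55% | 55% | 55% |
| 15 per arm: ANCOVA, week 8 | 67% | 62% | 59% | 57% |

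The ANCOVA rows ignore chance imbalance in baseline. Allowing for it lowers them by one to two points (20 per arm: 79, 74, 71 and 69%; 15 per arm: 65, 60, 58 and 55%). At ρ = 0.3 ANCOVA is also ahead of the main effect (about 84% v 74% with 20 per arm, sustained).

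**Two tests.** If a significant result on either counted as success, the type I error would be about 1 − 0.95² = 9.75%. Simulation at ρ = 0.7 gives 9.6% with 15 per arm and 9.9% with 20.

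**The case against.** The strongest reply is that the plan's follow-through rests on the interaction and not on the main effect: pairwise comparisons and effect sizes are tied to group-by-time. Because baseline is a response, the interaction compares change between arms, and the week-8 difference is one component of it. It is a valid randomised comparison, and its dependence on week 16 suits an objective that covers immediate and medium-term effects. Means and SDs are reported at each visit, so a difference in Barthel points can be worked out. An article may also leave model details to a fuller plan.

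Much of this stands. A reader might infer that efficacy will be claimed from the main effect; the text names that effect but nowhere says it counts as success. A reader might also infer that the type I error is nearly doubled. That needs an either-test rule, which the text neither states nor excludes. Nor is the interaction unrelated to the sizing.

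What does not fall away is that the article itself fixes the method, names two effects without ranking them, and makes the week-8 comparison conditional on an omnibus result and, as stated, unadjusted. That is a choice made in the text, not a detail left out of it.

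**Conclusion.** The concern holds as a mismatch between the sizing contrast and the named tests, with a better-matched alternative available from data already scheduled. The main effect is a poor measure of benefit here: it loses a third of a sustained effect and two thirds of one gone by week 16. The interaction is sound but unspecific, and it loses 12 to 13 points of power if half the benefit fades.

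Over correlations of 0.3 to 0.9, week-8 ANCOVA is above the main effect and at or above the change score. It is clearly above the interaction at lower correlations or when benefit partly fades. With a sustained effect it is about level with the interaction at 0.8 to 0.9, and slightly behind at 0.9, so the case there rests on having one interpretable estimate named in advance. It would be wrong to infer that the change is free or that it rescues the power: it moves week 16 to a secondary contrast, and at 15 evaluable per arm it stays below 80% throughout this range. All power figures rest on the assumed equal correlations and variances, normal data, and 3.10 being the SD of change, as the text says.

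**What to change.** Before the database is locked, amend the Statistical analysis section as follows.

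- Name one primary contrast: the between-arm difference in Barthel Index at week 8, adjusted for baseline Barthel Index, in points with a 95% CI. Fit it by ANCOVA, or as the week-8 contrast of a mixed model with weeks 8 and 16 as responses and baseline, arm, visit and arm-by-visit as terms.
- Report week 16 from the same model as the key secondary contrast, to serve the medium-term objective.
- State that the group main effect is not evidence of efficacy. Use the same model for the secondary scales.
- Restate the power in the Sample size section for this contrast, with a stated correlation. By normal approximation, 80% power needs 25.3 × (1+ρ)/2 per arm, where 25.3 = 2 × (3.10 × 2.80/2.44)²: about 20 at ρ = 0.5, 22 at 0.7 and 25 at 0.9, all evaluable.

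The analysis change needs new wording only, with no new data, and runs in the stated software. Its price is that week 16 is no longer part of the primary test. Restating the power will show that 15 evaluable per arm falls short, and the change of analysis alone does not resolve that.

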### Randomization and blinding

The patients who volunteer to take part in the study will be randomly allocated into two groups (the experimental and control groups), using a computational random number generator (EPIDAT 3.1, Xunta de Galicia) with randomization codes created by [name]. This will assign patients to a combined functional apraxia rehabilitation group or a control group with an allocation ratio (1:1). During the randomization process, patients will be blinded to their treatment allocation. The neurologist will examine the patients for eligibility criteria and collect all the baseline demographic variables but will not be involved in the rest of the study or preparation of the randomization codes. Treatment allocation will be concealed and patients and study personnel will be blinded to the treatment assignments until after the database has been locked. During the trial, all the outcome measures will be collected by three therapists, who will be blinded to the group allocation. Treatment interventions will all be carried out by an occupational therapist with wide clinical experience, who will be blinded to the outcome measures and baseline examination findings but not to the patients’ treatment allocation, although this allocation will not be revealed to the therapists who gather the outcome measure data. Criteria for receiving discontinued intervention will be as follows: 1) the participant requests voluntarily to miss any session, or 2) the interventions produce a significant improvement or worsening of apraxia disease. As part of the strategy to improve adherence to intervention, patients will be informed about the relevance of the treatment in each session, and they will be telephoned weekly to remind the date of the sessions. The final result of the study will be reported to the patients in both groups.

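### The Tukey follow-up does not suit two arms measured three times on the same patients, and Cohen's d for the interaction names no contrast, visit or SD

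*Protocol article*

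**What the plan says.** The Statistical analysis section of the protocol article plans a repeated measures ANOVA with an intervention effect and a time-by-treatment interaction. Where that interaction is significant, post hoc analyses are to be "carried out using the Tukey multiple comparison procedure to examine pairwise comparisons of the" two arms. The stated scope of these comparisons is "means for all outcome measures and across the three data collection times". The same section then gives the effect size for the group-by-time effect as Cohen's d, described as the "standardized difference between two means", with cut-offs of 0.2, 0.5 and 0.8 for small, medium and large.

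The article does not say how many means enter the Tukey procedure or which error term is used. It also does not say which visit or SD underlies d. The Sample size section rests on one quantity, a change score: "a clinically important difference pre-post treatment of 2.44 points on the Barthel Index for ADLs (primary outcome) was used to calculate" the number of patients, "assuming a standard deviation of 3.10 points for this difference and a two-sided test (α) of 0.05". Two arms are randomized 1:1, and the same patients are measured at baseline, 8 weeks and 16 weeks.

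**The concern.** Tukey's procedure is built for several independent means with a common error. Here there are two arms, and the three means within each arm come from the same patients. The procedure either has nothing to adjust (two arms at one visit) or is spread over 2 × 3 = 6 cells and 15 pairs, most of which nobody needs. In both cases it compares raw visit means and not change from baseline, although the trial is sized on change.

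This matters because the interaction test has 2 degrees of freedom and does not say at which visit the arms differ. The intervention main effect averages over baseline, when no treatment has been given. So the post hoc step is the only one that would answer the stated aims of an immediate and a medium-term effect. Cohen's d compares two means, and a three-visit interaction is not one difference of two means, so the planned effect size has no fixed value.

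**Working it through.** **Inputs.** From the Sample size section: difference 2.44, SD of change 3.10, two-sided alpha 0.05, 40 patients in total. With 1:1 allocation that is 20 per arm. The correlation between visits, ρ, is not in the article. It is assumed, equal for all pairs of visits, and ranged. The raw SD at one visit is then s = 3.10/√(2(1−ρ)): 3.10, 4.00 and 4.90 at ρ = 0.5, 0.7 and 0.8.

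**The plan's own figure.** The stated 15 per arm is not reproduced for a between-arm comparison: n = 2 × (1.960 + 0.842)² × (3.10/2.44)² = 25.3, so 26 per arm. A one-sample or paired t test with n = 15 has 80.9% power. This is a separate fault. It is noted here because it limits what any change of analysis can achieve.

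**Reading A: two arms compared at each visit.** With two groups, the Tukey critical value q(0.95; 2, 38)/√2 = 2.024 equals the t value on 38 df, so nothing is adjusted. The noncentrality is 2.44/(s√(2/20)) = 2.49, 1.93 and 1.57. Week-8 power is 68%, 47% and 34%. Ungated, the chance of at least one false difference over the three visits is 13% at ρ = 0.5 and 11% at ρ = 0.7.

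**Reading B: six cells, pooled cell error.** The critical value is q(0.95; 6, 114)/√2 = 2.90, against 2.02 for one t test. With the same noncentralities, power for the week-8 between-arm pair is 35%, 17% and 10%.

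**Reading C: six cells, within-subject error.** The within-subject mean square estimates s²(1−ρ), but the variance of a between-arm difference at one visit is 2s²/n. The test statistic is therefore inflated by 1/√(1−ρ) = 1.41, 1.83 and 2.24. By simulation with 20 per arm:

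| Setting | ρ = 0.5 | ρ = 0.7 | ρ = 0.8 |
|---|---|---|---|
| No true effect, interaction gate applied: any false between-arm difference | 2% | 3% | 3% |
| True effect of 2.44 at week 8 only, gate applied: false difference at baseline or week 16 | 6% | 13% | 21% |

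Once a real week-8 effect opens the gate, it no longer protects the other visits.

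**Interaction F test.** Its simulated rejection rate under the null is 5%. Its power is about 71% to 72% with 20 per arm, whether the 2.44-point benefit is sustained or present at week 8 only.

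**Baseline-adjusted contrast at week 8.** The residual SD is s√(1−ρ²) = 2.68, 2.86 and 2.94. The noncentrality is 2.87, 2.70 and 2.62 on 37 df. Power is 80%, 75% and 72%, and 70% at ρ = 0.9. With 15 evaluable per arm it is 67% at ρ = 0.5 and 57% at ρ = 0.9.

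**Cohen's d for the same 2.44 points.** On the change SD, 2.44/3.10 = 0.79. On the raw SD it is 2.44/s = 0.93, 0.79, 0.61 and 0.35 at ρ = 0.3, 0.5, 0.7 and 0.9. By the article's own cut-offs that runs from large to small.

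**The case against.** The best defence is that the main inference is the interaction test, and that test is sound. It uses within-patient change, holds 5% when sphericity holds (which the plan checks), and at 71% to 72% its power slightly exceeds the 68% of a t test on change. This stands. The plan as a whole does not discard within-patient information; only the follow-up step does.

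A reader might infer that the plan has uncontrolled false-positive rates, since under Reading C the chance of a false between-arm difference is 10%, 23% and 34% at ρ = 0.5, 0.7 and 0.8. Those rates arise only if the comparisons are run without the interaction gate. The article states the gate, and with it the rate under a global null is 2% to 3%. Inflation remains only when there is a real effect at one visit and the within-subject error is used.

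A reader might also take six cells and 15 pairs as what the article prescribes. It does not say so; comparing the two groups at each visit is an equally fair reading, and the 35%, 17% and 10% figures do not apply to it. That reading does not rescue the step, because Tukey is then empty and baseline is ignored.

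The error term and contrast coding may be set out in a fuller document, so their absence is not the fault here. The fault is the stated choice of procedure. Likewise d is not meaningless: for one named between-arm contrast with a named SD it is a proper effect size.

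**Conclusion.** The point holds as a misfit of the follow-up analysis, not as a failure of the primary test. Under each reading the Tukey step is an unadjusted comparison of raw means, a very conservative one, or one with the wrong error term for between-arm pairs. Against the raw-mean t test, the baseline-adjusted contrast gains about 12, 28 and 38 percentage points of week-8 power at ρ = 0.5, 0.7 and 0.8 (80−68, 75−47, 72−34). Against the six-cell pooled reading it gains 45, 58 and 62 (80−35, 75−17, 72−10).

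These figures assume 20 complete patients per arm, a true benefit of 2.44, an SD of change of 3.10, equal correlations between visits, and values of ρ that the article does not give. The logical points do not depend on ρ: Tukey with two groups is a t test, the interaction names no visit, and d needs a contrast and an SD. It would go too far to conclude that the change brings the trial to its stated 80%: with 15 evaluable per arm, power is 57% to 67% for ρ from 0.9 to 0.5.

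**What to change.** In the Statistical analysis section, replace the Tukey sentence with two named contrasts per outcome:

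- the baseline-adjusted between-arm difference at week 8, primary for the Barthel Index at two-sided alpha 0.05;
- the baseline-adjusted between-arm difference at week 16, secondary.

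Give each with a 95% confidence interval and report it whatever the interaction p-value. State that contrasts on the secondary outcomes are secondary and carry no confirmatory claim; otherwise removing Tukey and the gate would leave two contrasts on each of eight outcomes, 16 tests, with no stated status. Report Cohen's d only for these contrasts and name the SD used, for example the pooled baseline SD.

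The data are already collected at all three visits, so the cost is wording only. The sample-size calculation needs its own correction.

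### As written, RM ANOVA over three visits uses only patients with all three scores, so it does not deliver the intention-to-treat analysis promised for drop-outs

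*Protocol article*

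**What the plan says.** Under Research design, the protocol article states that "The main outcome measures will be collected at three time points over a 16-week period": baseline, week 8 and week 16. Under Statistical analysis, "The data obtained in this study will be analyzed with SPSS software, version 20.0", and for the intervention effect and the time-by-treatment interaction "repeated measures analysis of variance (RM ANOVA) will be conducted". Sphericity of the within-patient differences "will be analyzed with the Mauchly test and verified by the local invariant test".

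The same section closes with the promise that "Data from drop-outs and patients who discontinued intervention will be analyzed following an intention-to-treat principle".

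The Sample size section expects missing patients: "The sample size has been increased to a total of 40 to allow for a loss to follow-up of up to 22" per cent. No rule for a missed visit is named anywhere in the article.

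**The concern.** A drop-out is a patient whose later visits are missing. Classical RM ANOVA cannot use an incomplete set of scores, so the patients covered by the intention-to-treat sentence are the ones the named method removes. If the plan is followed literally, the Barthel result would be a complete-case analysis carrying an intention-to-treat label.

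Two things are at stake. First, observed data are discarded: someone seen at baseline and week 8 but not at week 16 drops out of the whole model, including the immediate post-treatment comparison. Second, the between-arm comparison may be biased if loss is related to response and the relation differs by arm. That is conceivable here because contact is so unequal: 3 sessions a week for 8 weeks (24) in the experimental arm against one workshop a month for 2 months (2) in the control arm.

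**Working it through.** **1. Which method is fixed.** The planned sphericity checks (the Mauchly test and the local invariant test) identify the method as classical RM ANOVA. A likelihood-based mixed model with unstructured covariance makes no sphericity assumption and would not call for them. Classical RM ANOVA needs all three scores per patient, and the SPSS repeated-measures procedure drops incomplete cases listwise. The article does not itself mention listwise deletion; it follows from the method it names.

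**2. The plan's own figure.** Inputs from the Sample size section: 15 per arm before inflation, loss up to 22%, total 40.
- 15 / (1 − 0.22) = 19.2, rounded up to 20 per arm, or 40 in total. The stated total reproduces.

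**3. Size of the analysis set at the maximum allowed loss.**
- Patients with all three visits: 40 × (1 − 0.22) = 31.2, about 31.
- Patients left out: 40 × 0.22 = 8.8, about 9.
- How many of these 9 would have a week-8 score depends on when they leave, which the article does not say. If half leave after week 8 (an assumption), about 4 observed week-8 Barthel scores are discarded.

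**4. Who is affected.** The promise covers two groups.
- Patients who discontinue the intervention but attend all visits have three scores. They stay in the RM ANOVA in their allocated arm, so there is no conflict.
- Patients with one or more missed visits are excluded. The mismatch concerns only them.

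**5. Illustration of possible bias.** None of the dropout inputs below comes from the article. Assumptions:
- Score SD 4.0 and correlation 0.7 between visits, so the SD of change is 4.0 × √(2 × (1 − 0.7)) = 3.10, matching the SD in the Sample size section.
- True mean gain of 2.44 in the affected arm.
- Loss in that arm only, all of it after week 8, with the odds of loss multiplied by exp(0.5) or exp(1.0) for each SD of poorer week-8 change.

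| Loss in the one arm | exp(0.5) per SD | exp(1.0) per SD |
|---|---|---|
| 22% | mean gain 2.77, shift 0.33 | mean gain 3.03, shift 0.59 |
| 11% | mean gain 2.61, shift 0.17 | mean gain 2.75, shift 0.31 |

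These are shifts in one arm's mean. They carry over in full to the between-arm difference only if the other arm has no loss or its loss is unrelated to response. If both arms lose patients by the same mechanism, the shifts cancel.

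The table also does not describe the 31-of-40 case in step 3. With 22% loss in one arm of 20 and none in the other, 4.4 patients are lost in total and about 36 of 40 are analysed.

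**The case against.** The strongest reply is that a journal article need not carry the missing-data rule. RM ANOVA on imputed data would include drop-outs, and the intention-to-treat sentence may presuppose some such step in a fuller document. Part of this stands: a reader might infer that the promised analysis is impossible under the stated method, and the article does not support that, because imputation before the ANOVA would reconcile the two statements. What remains is more than absent detail. The article fixes a method and makes a promise, and the method carried out as described does not fulfil it.

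A reader might also infer that the primary result will be overstated by a known amount, say 0.3 to 0.6 Barthel points. The article does not support that either:
- That range needs 22% response-related loss confined to one arm after week 8.
- 22% is an upper allowance, not a forecast.
- The direction is open, since the discontinuation criteria list both marked improvement and worsening.
- Weekly reminder calls, home delivery in both arms and the later offer of the programme to controls all work against differential loss.

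Finally, inflating from 15 per arm is an ordinary dropout allowance. It is not evidence that a completers' analysis was intended.

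**Conclusion.** The point holds in a limited form. As written, the primary method excludes every patient with a missed visit, while the same section promises that drop-outs are analysed by intention to treat. At the 22% ceiling, about 9 of 40 randomised patients would be left out, together with any week-8 Barthel scores they had already provided.

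This rests on reading the named method as classical RM ANOVA on the observed data, which the sphericity tests support, and on no imputation step being added. Bias is possible if loss is related to response and differs between arms; its size and sign cannot be derived from the document, and the illustrative shifts stand or fall with their assumptions. The mismatch concerns the analysis set for the primary outcome and is cheap to remove, so it should be settled before the data are unblinded.

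**What to change.** Replace RM ANOVA by a likelihood-based mixed model for repeated measures (SPSS MIXED, REML, unstructured covariance over the three visits, Satterthwaite degrees of freedom). Fit it to all observed visits of all randomised patients in their allocated arm. Keep baseline as one of the modelled outcomes rather than as a covariate, so that patients with no post-baseline visit also remain in the model. With an unstructured covariance, the Mauchly and local invariant tests can be deleted.

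An acceptable alternative is to keep RM ANOVA and apply multiple imputation first, stating the imputation model and how results are pooled.

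In either case, add one delta-adjusted sensitivity analysis for data missing not at random. State in the intention-to-treat sentence that patients who stop treatment are still to be assessed and analysed in their allocated arm.

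The cost is revised analysis wording and some programming. No new data, visits or patients are needed.
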